**Fig. 3 Fig3:**
[figure not shown]
Flowchart of the weekly step goals progression for patients in the intervention group. This protocol was based on Demeyer et al.^19^

### Outcome measures

#### Primary outcomes

##### Level of physical activity and sedentary behavior

It will be objectively measured by a triaxial accelerometer (Actigraph wGT3X-BT, Actigraph, Pensacola, FL, USA). The Actigraph wGT3X-BT will be initialized in a specific software (ActiLife v6.13.3) to collect data with a 60-hz sample rate. Participants will be instructed to wear the device on the waist (with an elastic belt) for 7 consecutive days. They should remove it only to perform water activities (i.e., showering) and sleep. This equipment provides as main variables the number of steps per day, time spent (in minutes and percentage of the day) in sedentary activities (<100 counts per minute), light-intensity PA (100–1951 counts per minute), and moderate to vigorous PA (≥1952 counts per minute) [20].

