**Methods:**

This double-blind clinical trial will investigate the effectiveness of an online behavior change intervention in increasing physical activity and reducing sedentary behavior in adults with asthma, as well as in improving other clinical outcomes in short and medium terms. Patients with clinically stable moderate to severe asthma, who are physically inactive and do not have cardiovascular and/or osteoneuromuscular impairments will be randomized into control or intervention groups (23 in each). Both groups will carry out an online educational program (1 h). Additionally, the intervention group will receive weekly individual online sessions for 12 weeks of motivation-based behavior change intervention to promote an increase in physical activity and reduce sedentary behavior based on both self-determination theory and transtheoretical model. The intervention group will also receive an activity monitor with specific strategies related to it. Both groups will be reassessed immediately after the intervention and 6 months after that. The primary outcomes are physical activity and sedentary behavior, which will be objectively assessed by a triaxial accelerometer (Actigraph wGT3X-BT). Secondary outcomes are Asthma Control Questionnaire, Incremental Step Test, Sit-To-Stand, Timed Up-and-Go, 4-Metre Gait Speed, Asthma Quality of Life Questionnaire, Pittsburgh Sleep Quality Index, Epworth Sleepiness Scale, Actiwatch 2, and the Hospital Anxiety and Depression Scale.

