## Methods

### Aims

The primary aim of this randomized clinical trial is to investigate the effectiveness of an online BC intervention based on both SDT and TTM in increasing PA and reducing sedentary behavior in adults with asthma. Secondary aims are (I) to observe the impact of this intervention on asthma control, functional capacity, quality of life, sleep quality, and symptoms of anxiety and depression; (II) to verify whether the BC intervention improves the satisfaction of BPNs, self-determination and autonomous forms of motivation for PA; and (III) to investigate if the effects of the BC intervention will be maintained in the medium term (6 months after the end of intervention).

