### Sample size calculation

The sample calculation was based on a previous study with adults with asthma in which two groups performed a 12-week intervention to increase physical activity, and the number of steps/day obtained in both groups (control and experimental) were normally distributed with the following values after the intervention: 6248±2030 and 8853±3320 steps/day, respectively [11]. Therefore, for the present study, a total sample of 38 people will be needed to reject the null hypothesis, with a power of 0.8 and a value of *P*<0.05. However, considering a 20% drop-out rate [13] throughout the study, the final sample size will be 46 people (23 in each group).

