### Statistical analysis

Statistical analysis will be performed after post-intervention and follow-up assessments using the software SPSS Statistics V22.0 (IBM, USA). Data distribution will be analyzed using the Shapiro-Wilk test. Variables will be presented as mean (SD), median [interquartile range 25–75%] according to data distribution. Categorical variables will be presented as absolute and relative frequency. The magnitude of statistical estimates will be presented using 95% CI. The results will be analyzed according to the intention-to-treat principle, as recommended by the CONSORT statement [40]. Per-protocol analysis might be performed to contrast results. Mixed model ANOVA will be used to identify the effect of the protocol to promote physical activity and reduce sedentary behavior. The repeated measures factor will be “time” (pre- and post-intervention evaluation) and the independent measures factor will be the “group” (control group or intervention group). To compare the proportion of patients that achieved the minimal clinical important difference in ACQ and AQLQ (0.5 points for both) [22, 41] between groups, the chi-square test will be used. Pearson or Spearman correlation coefficients will be used to verify the relationship between the changes in PA and changes in asthma control or quality of life. Values of *P* <0.05 will be considered statistically significant.

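### Physical activity and sedentary behavior are both primary, with no lead variable, test order or success rule, and the sample size covers steps/day only

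*Protocol article*

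**What the plan says.** - **Abstract, Methods:** "The primary outcomes are physical activity and sedentary behavior, which will be objectively assessed by a triaxial accelerometer".
- **Aims:** the primary aim concerns effectiveness "in increasing PA and reducing sedentary behavior in adults with asthma". How the two parts combine into a successful trial is not stated.
- **Primary outcomes, Level of physical activity and sedentary behavior:** "This equipment provides as main variables the number of steps per day, time spent (in minutes and percentage of the day) in sedentary activities", followed by "light-intensity PA (100–1951 counts per minute), and moderate to vigorous PA (≥1952 counts per minute"). That makes four measures, three of them in two units, and none is named as the lead.
- **Statistical analysis:** "Mixed model ANOVA will be used to identify the effect of the protocol to promote physical activity and reduce sedentary behavior". The factors are time (pre and post) and group. The section closes with one general threshold: "Values of *P* <0.05 will be considered statistically significant". It gives no order and no rule on whether one or both constructs must succeed.
- **Sample size calculation:** the inputs come from an earlier asthma trial in which "the number of steps/day obtained in both groups (control and experimental) were normally distributed": 6248±2030 and 8853±3320. This gives 38 people at power 0.8, raised to 46 for drop-out. No effect, SD or power is given for sedentary time or any intensity band.

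**The concern.** The stated 0.05 and 0.8 belong to a single test of steps/day, whereas the declared primary question has two parts. The text leaves two readings open, and each undermines one of the two figures.

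If a significant result on either construct is enough, the primary-level error exceeds 5%. It rises further if physical activity may be represented by steps, light time or moderate-to-vigorous time. If both constructs must improve, the error is controlled but the trial has less than 0.8 power for its primary claim.

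The practical risk is that the reading, or the variable standing for physical activity, is settled after the results are known.

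**Working it through.** **1. Reproducing the 38.**
Inputs, from Sample size calculation: means 6248 and 8853, SDs 2030 and 3320, power 0.8, alpha 0.05 (two-sided assumed; sidedness is not stated).
- Difference: 8853 − 6248 = 2605.
- Pooled SD: √[(2030² + 3320²)/2] = 2751.7.
- d = 2605 / 2751.7 = 0.947.
- The exact two-sided two-sample t test needs 19 per arm, 38 in total, with power 0.81 (18 per arm gives 0.79).

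The plan's figure is reproduced. Its only inputs are steps/day.

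**2. If any one significant result counts.**
With k independent tests at 0.05, the chance of at least one false positive is 1 − 0.95^k.
- k = 2: 1 − 0.95² = 9.75%.
- k = 4: 1 − 0.95⁴ = 18.5%.

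The measures come from one device worn on the same days, so they are correlated and these are upper values. The document gives no correlations. Simulation (1,000,000 multivariate normal draws, equal correlation r assumed) gives:

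| r | 2 outcomes | 4 outcomes |
|---|---|---|
| 0.3 | 9.5% | 17.4% |
| 0.5 | 9.1% | 15.6% |
| 0.7 | 8.4% | 13.1% |
| 0.9 | 7.0% | 9.4% |

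These are two-sided rates. Counting only the favourable direction, the independent values are 1 − 0.975² = 4.9% and 1 − 0.975⁴ = 9.6%, to be set against 2.5% for one test.

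**3. If both constructs must succeed.**
Type I error stays at or below 5%. For power, assume that sedentary time has the same d = 0.947 at 19 per arm, with correlation taken in the direction of benefit.
- Noncentrality: 0.947 / √(2/19) = 2.918.
- Normal approximation: power per outcome is Φ(2.918 − 1.960) = 0.831. Joint power is 0.831² = 0.69 at r = 0 and 0.75 at r = 0.7 (bivariate normal).
- t test, as in step 1: power per outcome is 0.810. Joint power is 0.810² = 0.66 at r = 0 and 0.73 at r = 0.7.

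Both ranges lie below 0.8. The t-based range is the one consistent with the reproduced 38.

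**4. Sedentary time on its own.**
With 19 per arm, 80% power requires d of about 0.94. Over an assumed range, power is 0.32 at d = 0.5, 0.56 at d = 0.7 and 0.67 at d = 0.8. Joint power cannot exceed the power of sedentary time alone, so a smaller effect there would push it below the ranges in step 3.

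**The case against.** **An unseen analysis plan may supply the order and the success rule.** This is fair for the details of multiplicity control. But this document itself fixes two primary constructs under one threshold and sizes for one variable. The mismatch is in what is stated.

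**The aim is conjunctive, so error may not inflate.** This stands as one of the two readings. The any-one-wins percentages apply only to the other reading. The document does not choose, and under the conjunctive reading the 0.8 is not reached.

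**The 0.8 is tied to steps/day, and steps drive the weekly goals, so the lead variable can be guessed.** The first part is correct: the Sample size calculation claims no power for sedentary time, and its arithmetic is sound. An inferred lead variable is still not a pre-specified one.

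**Stronger readings that the text does not support.** A reader might count seven primary results, because three measures are given in minutes and in percentage. The two units re-express one quantity, so they are not separate hypotheses. The sentence also describes what the device provides. A reader might also infer that every measure is tested separately at 0.05. The Statistical analysis section lists no test per variable; it names one analysis for the two constructs and one general threshold. The two-outcome case therefore rests firmly on the text, while the four-outcome case depends on how the listed measures are used. A loss of power from splitting alpha would not measure the problem either, since the plan proposes no split.

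**Conclusion.** The point holds as a gap between the declared primary question and the error rate and power attached to it. The 38 itself is correct for steps/day.

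If any one result suffices, the primary-level error is about 7–10% for two outcomes and 9–18% for four, under assumed equal correlations from 0.9 to 0. If both constructs are required, error is controlled. Joint power at 38 evaluable is then about 0.69–0.75 (normal approximation) or 0.66–0.73 (t test), for assumed correlations of 0 to 0.7. Those power figures depend on borrowing the steps/day effect size for sedentary time, which the document does not justify.

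The equal-correlation model is a simplification, since the three intensity bands divide the same measured time. Nothing here shows that any result has been selected after the fact; the wording leaves room for it.

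**What to change.** Before analysis:

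1. Name one variable per construct at the post-intervention assessment: steps/day for physical activity, and sedentary time in one of the two units already listed.
2. Test them in fixed sequence at two-sided 0.05: steps/day first, and sedentary time only if steps/day is significant.
3. Treat light activity, moderate-to-vigorous activity and the alternate units as secondary.
4. State that the 0.8 power applies to steps/day only.
5. Report this as a protocol change, which the Ethics section already commits to doing.

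A fixed sequence keeps the primary-level error at 5% without splitting alpha, and the planned 46 can stay. Sedentary behavior can remain a primary outcome, second in order. Removing its primary status is not needed and would be harder to defend, because recruitment began in February 2022. The cost is that sedentary time cannot be claimed as a confirmatory result if steps/day fails.

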#### Secondary outcomes

##### Asthma control

The validated Asthma Control Questionnaire (ACQ) [21] on its 6-item version [22] will be applied. Participants must recall their symptoms during the previous week and answer the first 6 questions on a 7-point scale, ranging from 0 (no impairment) to 6 (maximum impairment) [23]. Items are equally weighted and the score is the average of all items.

##### Asthma symptoms and medication control diary

Patients will be given a paper diary in which they must record the asthma symptoms and exacerbations, as well as the use of medications for the disease during the 3 months of intervention [24]. Exacerbations will be defined as the use or increment of oral corticosteroids, for at least 3 days, due to worsening of symptoms; need for a doctor’s appointment or emergency care due to worsening of symptoms; or rescue bronchodilator use 4 times or more within 24 h for 2 consecutive days [25].

##### Functional capacity

Four different tests will be used: Incremental Step Test (IST), Sit-To-Stand (STS), Timed Up-and-Go (TUG) and 4-Metre Gait Speed (4MGS). All of them will be performed twice with a minimum rest period of 30 min and the best result will be used for analysis [26, 27]. To perform the IST, participants will be instructed to go up and down a step (20cm high, 40cm wide, 60cm deep). The cadence will be determined by an audio signal with an initial rhythm of 10 steps/min and will have increments of 1 step every 30 s until the participant’s tolerance. The result will be given both in the number of steps and in the vertical distance [27].

The STS will be performed in two different protocols: the 1-min (result in the number of repetition) and the 5-repetitions (result in seconds). Patients will be instructed to begin seated in a 46-cm high chair, with their arms crossed over the chest. With the command “go,” they will have to get up immediately and sit down repeatedly [26].

To perform the TUG, patients will be instructed to get up from a chair in the command “go,” walk in a straight line of 3 m on the floor, turn around, walk back to the chair and sit down. The time to perform the test at both normal and fast speeds will be counted [26].

In the 4MGS, the patients must walk a distance of 4 m marked on the floor, at the usual speed. The time, in seconds, needed to perform this activity is counted from the moment the patient starts to move until the moment the first foot completely crosses the 4-m line [26].

##### Quality of life

The validated Asthma Quality of Life Questionnaire (AQLQ) will be applied. Individuals should recall the frequency, intensity, and severity of health difficulties they have had due to asthma in the past 2 weeks. The total score is the emerging average of responses on 32 items on a seven-point scale, under four domains: activity limitations, symptoms, emotional function, and exposure to environmental stimuli. The score for each domain separately emerges from the average of their respective items [28].

##### Sleep assessment

Sleep quality will be assessed by the Pittsburgh Sleep Quality Index. This validated questionnaire consists of 19 questions regarding the last month, categorized into 7 components, classified between 0 and 3, with a total score ranging from 0 to 21 [29]. Daytime sleepiness will be assessed using the Epworth Sleepiness Scale, a questionnaire that assesses the probability of napping in 8 situations involving daytime activities. The total score ranges from 0 to 24 [30].

The Actiwatch 2 (Philips Respironics, Murrysville, Pennsylvania, USA) will be used to objectively measure sleep quality. This device must be used on the wrist of the non-dominant hand for 7 consecutive days, 24 h a day (the same period of use as the Actigraph, mentioned previously) [31]. During the days of use, patients must report in a diary information about bedtime, waking up, daytime nap time, and day/night-time symptoms. The following sleep variables will be measured: total time in bed, total sleep time, onset latency, sleep efficiency, wake after sleep onset, and the number of awakenings [31].

##### Anxiety and depression

Patients will answer to the Hospital Anxiety and Depression Scale [32]. This is a valid and simple 14-item questionnaire, with half of the items referring to anxiety and the other half to depression. Each item is rated on a 4-point scale, which gives a maximum subscale score of 21 for anxiety and depression, respectively [33].

##### Basic psychological needs

The Basic Psychological Needs in Exercise Scale will assess the participants’ perceptions of meeting basic psychological needs and exercise satisfaction. This validated scale consists of 12 items divided into three domains: autonomy, competence, and relatedness. The answers for each item range from 1 (I don’t agree) to 5 (I completely agree) [34].

##### Motivational regulations

The Behavioral Regulation in Exercise Questionnaire (BREQ-3) will be used to assess participants’ motivational regulations (amotivation, external, introjected, identified, integrated, and intrinsic regulation) to exercise/PA. This validated questionnaire consists of 23 items ranging from 0 (not true) to 4 (very true for me). The score is calculated for each motivational regulation as well as for the self-determination index [35].

##### Lung function

The assessment of lung function will be performed after the use of a bronchodilator using a spirometer (Pony FX COSMED, Italy). The technique will be performed according to the guidelines of the American Thoracic Society [36], determining the FEV_1_, forced vital capacity (FVC), and FEV_1_/FVC index. Reference values for the Brazilian population will be used [37].

##### Sociodemographic and anthropometric assessments

To characterize the sample, general data will be collected such as age, smoking habits, and personal history. Self-report of general comorbidities will be assessed by the validated Charlson index [38], and the most common comorbidities for people with asthma [39] will be questioned. Participants’ height and body weight will be objectively measured and the body mass index (BMI) will be obtained.

### Sample size calculation

The sample calculation was based on a previous study with adults with asthma in which two groups performed a 12-week intervention to increase physical activity, and the number of steps/day obtained in both groups (control and experimental) were normally distributed with the following values after the intervention: 6248±2030 and 8853±3320 steps/day, respectively [11]. Therefore, for the present study, a total sample of 38 people will be needed to reject the null hypothesis, with a power of 0.8 and a value of *P*<0.05. However, considering a 20% drop-out rate [13] throughout the study, the final sample size will be 46 people (23 in each group).

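### The 38 evaluable, 20% drop-out and 46 randomised do not fit together: 46 leaves about 37 evaluable, a small shortfall that needs restating

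*Protocol article*

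**What the plan says.** In the protocol article, under Sample size calculation, the post-intervention steps/day of an earlier asthma trial, control then experimental, are given as "6248±2030 and 8853±3320 steps/day, respectively [11"]. From these the section concludes that "a total sample of 38 people will be needed to reject the null hypothesis, with a power of 0.8" at a 5% significance level. It then allows for losses: "considering a 20% drop-out rate [13] throughout the study, the final sample size will be 46 people (23 in each group"). The inflation formula is not written out, and the sidedness of the test is not stated. The Abstract repeats 23 per group. Nothing elsewhere in the article changes or explains the step from 38 to 46.

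**The concern.** A drop-out rate is a fraction of those who enter the trial. To keep a required number after losing 20%, that number is divided by 0.8. The printed total matches multiplication by 1.2, which gives a smaller result. If so, the trial at its own planning drop-out rate would be expected to finish with fewer evaluable people than the number it says it needs. At stake is whether the size, the drop-out allowance and the power claim can be reported together as they stand. Any reader of the results paper can check this from three printed figures.

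**Working it through.** **Inputs**, all from Sample size calculation: means 6248 and 8853 steps/day, SDs 2030 and 3320, power 0.8, significance level 0.05, 38 evaluable, 20% drop-out, 46 randomised in two equal groups. Assumption: a two-sided test. It is the choice that reproduces 38; a one-sided test would need only 30 in total.

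**Step 1: reproduce the 38.**
- Difference: 8853 − 6248 = 2605.
- Pooled SD: √((2030² + 3320²)/2) = √7,571,650 = 2751.7.
- Standardised difference: 2605/2751.7 = 0.947.
- Power of the two-sample t-test (noncentral t): 0.788 with 18 per arm and 0.810 with 19 per arm.

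The smallest equal-arm size that reaches 0.80 is therefore 19 per arm, or 38 in total, as printed. The unequal-variance (Welch) version agrees: 0.783 with 18 per arm and 0.806 with 19.

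**Step 2: reproduce the 46.**
- 38 × 1.2 = 45.6, rounded up to 46. This matches the printed figure, but the multiplication is inferred.

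**Step 3: apply the stated drop-out rate.**
- Needed to keep 38: 38/(1 − 0.20) = 47.5, so 48. Per group: 19/0.8 = 23.75, so 24.
- Expected to remain from 46: 46 × 0.8 = 36.8, or 23 × 0.8 = 18.4 per group.
- Expected to remain from 48: 48 × 0.8 = 38.4.
- Largest loss from 46 that still leaves 38: (46 − 38)/46 = 8/46 = 17.4%.

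**Step 4: what it does to power** (same standardised difference, two-sided 0.05, unadjusted comparison).

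| Evaluable | Power |
|---|---|
| 18 + 18 | 0.788 |
| 18.4 per arm (the expectation) | 0.797 |
| 18 + 19 | 0.799 |
| 19 + 19 | 0.810 |

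At the expected number remaining, power is 0.797. That is 0.013 below the figure for 38 evaluable and 0.003 below 0.80.

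**The case against.** The best defence is that the error hardly matters. Power is stated to one decimal, and every value from 18 + 18 to 19 + 19 rounds to 0.8. So 46 randomised, 20% loss and power of 0.8 do hold together at the printed precision; only the 38 in between does not fit. This stands, and it limits the point to an inconsistency among 38, 20% and 46.

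It can also be said that 46 has another possible origin. The normal approximation gives 18 per arm, or 36, and 36/0.8 = 45, rounded to 46 for equal arms. But the section prints 38 as its base, so this does not reconcile the printed figures. It is a reason to treat the multiplication by 1.2 as likely rather than established.

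Third, drop-out need not mean a lost outcome. Design and setting says that people who stop the intervention will be invited to a follow-up assessment, and Statistical analysis adopts intention-to-treat. This softens the consequence, since more than 36.8 may be measured. It does not repair the arithmetic, because the section itself chose to inflate for drop-out.

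Two stronger readings are tempting, and the article supports neither:
- A reader might infer that the 6-month assessment has no reserve because losses accumulate. The 20% is stated to apply throughout the study, so those losses are already inside it. The planned mixed model compares pre- and post-intervention, and maintenance at 6 months is a secondary aim. No separate 12-week loss rate is given. Loss by 12 weeks cannot exceed the whole-study figure and may be below 17.4%.
- A reader might infer that adjusting for baseline would win back the lost power. That depends on a pre-post correlation that the article does not give.

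**Conclusion.** The concern holds in a limited form. The 38, the 20% and the 46 cannot all be right: 20% loss calls for 48 randomised, while 46 covers a loss of 17.4%. The shortfall is 2 randomised participants (1 per group), and about 1 to 2 percentage points of power compared with 38 evaluable. The base figure of 38 is sound; only the inflation step fails.

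A reader might conclude that the trial is underpowered. The figures do not support that, because power stays at about 0.79 to 0.80 at the stated drop-out rate.

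The inconsistency among the three printed figures needs no assumption beyond reading the drop-out rate as a share of those randomised. The power figures also rest on a two-sided 5% test, the earlier trial's means and SDs, an unadjusted two-group comparison, and everyone who drops out lacking an outcome.

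**What to change.** Restate the figures and leave enrolment as it is. For example: 46 randomised with 20% drop-out leaves about 36 to 37 evaluable and power of about 0.79 to 0.80 for an unadjusted comparison; 38 evaluable is retained only if drop-out is at most about 17%. Add that the test is two-sided, if that was the intention.

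The cost is one corrected sentence and a slightly less favourable stated power. Design, conduct and analysis do not change. The Ethics section already commits to reporting protocol changes in the results article, so the correction can be made there.
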